## Abstract

**Background:**

The number of older adults living with lower limb amputation (LLA) who require rehabilitation for improving their walking capacity and mobility is growing. Existing rehabilitation practices frequently fail to meet this demand. Nintendo Wii Fit may be a valuable tool to enable rehabilitation interventions. Based on pilot studies, we have developed “Wii.n.Walk”, an in-home telehealth Wii Fit intervention targeted to improve walking capacity in older adults with LLA.

**Objective:**

The objective of this study is to determine whether the Wii.n.Walk intervention enhances walking capacity compared to an attention control group.

**Methods:**

This project is a multi-site (Vancouver BC, London ON), parallel, evaluator-blind randomized controlled trial. Participants include community-dwelling older adults over the age of 50 years with unilateral transtibial or transfemoral amputation. Participants will be stratified by site and block randomized in triplets to either the Wii.n.Walk intervention or an attention control group employing the Wii Big Brain cognitive software. This trial will include both supervised and unsupervised phases. During the supervised phase, both groups will receive 40-minute sessions of supervised group training three times per week for a duration of 4 weeks. Participants will complete the first week of the intervention in groups of three at their local rehabilitation center with a trainer. The remaining 3 weeks will take place at participants’ homes using remote supervision by the trainer using Apple iPad technology. At the end of 4 weeks, the supervised period will end and the unsupervised period will begin. Participants will retain the Wii console and be encouraged to continue using the program for an additional 4 weeks’ duration. The primary outcome measure will be the “Two-Minute Walk Test” to measure walking capacity. Outcome measures will be evaluated for all participants at baseline, after the end of both the supervised and unsupervised phases, and after 1-year follow up.

**Results:**

Study staff have been hired and trained at both sites and recruitment is currently underway. No participants have been enrolled yet.

**Conclusions:**

Wii.n.Walk is a promising in-home telehealth intervention that may have useful applications for older adults with LLA who are discharged from rehabilitation or live in remote areas having limited or no access to existing rehabilitation programs.

**Trial Registration:**

Clinicaltrial.gov NCT01942798; http://clinicaltrials.gov/ct2/show/NCT01942798 (Archived by WebCite at http://www.webcitation.org/6V0w8baKP).

##  Introduction

In 2003, it was estimated that more than 2 million individuals were living with lower limb amputation (LLA) in North America with an annual incidence of 150,000 [1]. Over half of LLAs are transtibial (TT) and transfemoral (TF) amputations [2]. In Western countries, the incidence of LLA increases sharply after the age of 50 years as a result of secondary complications associated with illnesses such as diabetes and vascular disease [2].

Recovery following LLA is notably slow. A lengthy recovery process is especially common among older adults who often have multiple co-morbidities including peripheral vascular disease, peripheral neuropathy, hypertension, heart disease [3,4], and cognitive impairment [5]. LLA, compounded with these co-morbidities, influences walking and places these individuals at a high risk of falling and sustaining injury after a fall [6]. In fact, 52% of community-dwelling individuals with LLA report falling each year [7]. Similarly, 49% have a fear of falling and 65% report low balance confidence [7]. The consequences associated with these numbers may contribute to deterioration in balance [8], endurance, strength, and coordination [9] in older adults, and ultimately a decline in walking capacity. Walking capacity is a strong determinant of health-related quality of life (HRQOL) in individuals with LLA [10-13] as well as the best predictor of prosthetic walking in individuals with LLA [14]. The ability to walk longer distances allows the individual to move around his or her environment independently, which in turn impacts one’s choice of activities and participation [15].

Following an LLA, individuals need to participate in prosthetic rehabilitation. Rehabilitation includes procurement of a prosthetic limb and ambulation training. The costs associated with post-amputation care and prosthetic rehabilitation are considerable. Post-LLA, projected lifetime health care costs total approximately US $509,000 [16]. Due to escalating costs, existing rehabilitation programs are experiencing difficulty providing sufficient levels of prosthetic therapy [1]. Furthermore, a trend toward outpatient rehabilitation, community inaccessibility, and transportation barriers imposes challenges for clients, particularly those in rural/remote areas, to attend face-to-face clinic appointments [17]. Therefore, accessible and innovative approaches are needed to improve outcomes for individuals with LLA and overcome these barriers to participation.

In-home telehealth is an innovative and emerging approach to provide rehabilitation through technologies and telecommunication [17-20]. Home treatments create accessible rehabilitation programs, promote continuity of care after discharge, and offset the time and expense of travel for clients to in-hospital rehabilitation programs [21,22]. Access to in-home rehabilitation is particularly important for those with limited access to facilities and transportation [23].

Nintendo Wii Fit is a commercial gaming technology that shows promise as an in-home rehabilitation tool. The benefits of using Wii Fit technology as a rehabilitation tool are demonstrated by the growing knowledge base on the use of gaming technology in older adult rehabilitation. In a study of older adults that used Wii Fit during in-patient rehabilitation, more than 80% expressed their desire to continue using Wii Fit at home [24]. Preliminary evidence suggests Wii Fit training is a feasible and safe method leading to improvements in balance [25,26], walking [25-27], and balance confidence in older adults [27]. Studies have reported improvements in walking and balance confidence in individuals with multiple sclerosis [28] and improved balance and decreased risk of falls in individuals with mild Alzheimer’s [29]. Pilot testing has shown improvements in balance, balance confidence, and gait variables [25] in two older adults with LLA, which is consistent with findings from our own pilot work [30].

In a Single Subject Research Design (SSRD) study of six individuals with LLA, the feasibility of a Wii Fit oriented intervention consisting of structured daily training varying from 2 to 6 weeks was assessed. Results indicated a statistical improvement in walking capacity in five participants who had 3 or more weeks of intervention [30]. The aim of the present study is to extend findings on this topic and conduct a randomized controlled trial (RCT) to assess our in-home telehealth Wii Fit intervention protocol we call “Wii.n.Walk” *(*Clinicaltrial.gov NCT01942798).

The primary clinical hypothesis is that participants in the Wii.n.Walk intervention group will experience an improvement in walking capacity compared to the control group. The secondary clinical hypothesis is that participants in the Wii.n.Walk intervention group will experience an improvement in lower limb functioning (balance, gait speed, and strength), dynamic balance, physical activity, and balance confidence. The tertiary clinical hypothesis suggests that the Wii.n.Walk group will experience an improvement in life space mobility, prosthetic use, HRQOL, and will have a lower incidence of falls. The adherence hypothesis is that the Wii.n.Walk group will have ≥80% adherence.

## Methods

### Trial Design

A parallel, evaluator-blind RCT conducted at two sites (Vancouver, British Columbia and London, Ontario) will be used. To minimize participants’ bias associated with knowing which intervention is of interest to researchers, we will attempt to mask participants to the true study objectives (NCT01942798). This will be achieved thorough stating that “evidence suggests that having good cognition improves physical outcomes and we are trying to determine whether cognitive or activity training is better” both in the consent form and when addressing subjects’ comments/questions.

Participants will be stratified by site and block randomized to the Wii.n.Walk intervention or control group in triplets using a 1:1 allocation ratio. To ensure balance between groups and masking of group assignment, a central computerized randomization process will be designed by the research team statistician, with undisclosed variable block sizes. Randomization will occur after the participant is screened and enrolled (Figure 1). The site coordinators will contact the statistician via telephone or email and obtain group assignment. The participant’s contact information will be forwarded to the appropriate group trainer to arrange for an initial training session.

This trial includes a supervised and an unsupervised phase for both the Wii.n.Walk intervention and control group. Once enrollment has been completed, participants will be evaluated on a number of clinical measures at baseline, after the supervised phase is completed, after the unsupervised phase is completed, and at a 1-year follow-up time point.

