### Participants

A total of 72 community-dwelling prosthetic ambulators in London and Vancouver will be recruited through clinicians and prosthetists. A letter of information will be distributed to all individuals in the amputee program databases who meet the study inclusion criteria. Participants need to be ≥50 years of age, have a unilateral TT or TF amputation, use their prosthesis for at least 2 hours per day for the past 6 months to minimize the influence of residual limb/prosthetic fit problems, be cognitively able to engage in the program (receive a score on the Modified Mini-Mental Status Exam score of >23) [31], and have a television that will enable connection to the Nintendo hardware.

Individuals will be excluded if they cannot communicate in English, cannot provide informed consent, have medical conditions (eg, congestive heart failure) that limit exercise participation as determined using the American College of Sports Medicine exercise guidelines for older adults [32], have prosthetic fit issues (eg, pain and discomfort) as indicated by scores <6 on the Prosthetic Socket Fit Comfort Scale [33], or are currently participating in another supervised exercise or training program (eg, balance training).

Participants between 50-69 years old will be medically screened by the site coordinators using the Physical Activity Readiness Questionnaire (PAR-Q) [34]. Participants who are 70 or more years old or who answer “yes” to any of the PAR-Q questions will be medically screened by a physician using the Physical Activity Readiness Medical Examination (PARmed-X) to obtain clearance for physical activity participation [35].

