### Outcome Evaluation

#### Overview

Outcomes will be evaluated (Figure 1) by blinded evaluators at baseline, end of the supervised phase (week 5), end of the unsupervised phase (week 10), and end of retention period (week 62). The evaluators will be senior university students in health sciences and will have at least 1 year of experience working with research participants. They will be trained by co-investigator, BI, who has more than 5 years of experience working with amputees and administering the outcome measures used in this study.

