### Limitations

This study has a number of limitations. RCTs in rehabilitation are subject to numerous threats to study validity [87]. First, blinding is a difficult limitation to overcome. Evaluators will be blinded and will request the participants not reveal their group status. We will also endeavor to mask participants to the true study objectives. It still may be evident which intervention is of primary interest based on the outcomes used. Therefore, we attempt misdirection by including the WWT test and by stating that “We are trying to determine whether cognitive or activity training is better for improving function” both in the consent form and when addressing participants’ comments/questions. Second, contamination and co-intervention will be difficult to control because the Wii Fit and the Big Brain are commercially available. While masking study objectives may reduce these risks, we will also conduct the in-clinic sessions at different times during the day so that participants will not have contact with the other group. Third, although the trainers will ask the participants not to use the treatment software outside of the treatment schedule, they may ignore these requests. Date/time stamped Wii use data downloaded at the end of intervention from the consoles will be assessed to determine adherence. This will also enable us to explore if individuals other than the participant used the Wii. Fourth, not everyone likes video games; however, the pilot work and the Wii Fit literature [72] suggest that the majority of older participants enjoy the games. Fifth, there is a possibility for a technology burden, particularly for older participants. We endeavored to simplify the technology used in this study to minimize the burden. We will use color-coded dots to highlight important buttons on the iPads, headphones, and the Wii consoles, so it will be easier for participants to locate them. Participants will be trained on how to use each piece of the technology during their in-clinic sessions as well as during the equipment set up at their homes. They will also be provided with a take-home manual that clearly explains step-by-step guidelines for using the program. In case participants have difficulty connecting with the trainer during the supervised phase, the trainer will troubleshoot remotely by telephoning participants. Sixth, our sample will represent older adult volunteers. The results will not be generalizable to younger amputees. We do not view this as a limitation given that >80% of individuals with LLA in Western countries are older adults. The results will be limited to differences related to older volunteers. Finally, loss to follow-up is a threat, particularly when participants are based remotely. To minimize loss to follow-up, the site coordinators will maintain contact with participants once a month upon termination of the unsupervised phase under the premise of collecting information on falls.

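### Site coordinators screen entrants, receive the group assignments and collect falls information; unless each triplet is full before release, up to 48 of 72 arms are known in advance to someone who screens.

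*Protocol article*

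**What the plan says.** **Allocation (Trial Design).** Participants are stratified by site and "block randomized to the Wii.n.Walk intervention or control group in triplets using a 1:1 allocation ratio". The list is central and computer-generated, and its block sizes vary and are not disclosed. Randomization follows the screening and enrollment of the participant, in the singular. Then: "The site coordinators will contact the statistician via telephone or email and obtain group assignment". The participant's contact details go on to the trainer of the assigned group.

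**Screening (Participants).** Those aged 50-69 "will be medically screened by the site coordinators", using the PAR-Q. A physician clears everyone aged 70 or over and anyone with a positive PAR-Q answer.

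**Falls.** A lower incidence of falls in the Wii.n.Walk group is part of the tertiary hypothesis (Introduction). The Fall Calendar records number, circumstances and consequences through the study (Tertiary Outcome Measures); the article does not say who completes it. In the unsupervised phase the trainer telephones weekly and asks about safety, including falls (Wii.n.Walk Intervention). Afterwards, "the site coordinators will maintain contact with participants once a month upon termination of the unsupervised phase", with falls information as the stated reason for the contact (Limitations).

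**Blinding (Outcome Evaluation, Overview).** "Outcomes will be evaluated (Figure 1) by blinded evaluators" at baseline and at weeks 5, 10 and 62. The evaluators are senior students, a separate role from the coordinators.

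**The concern.** Two risks follow from this overlap of tasks.

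1. **Selection.** A person who screens should not know, or be able to work out, the arm the next entrant will join. Where three places share one arm, revealing the arm for the first place reveals it for the other two. A coordinator could then, even unintentionally, steer, delay or discourage a candidate.
2. **Ascertainment of falls.** What counts as a fall, and what is recorded about its cause and consequences, depends on participant report and on prompting. If those who ask know the arm and the hypothesis has a direction, the comparison can be biased.

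**Working it through.** **Do members of a triplet share an arm?** Supervised sessions run in groups of three (Wii.n.Walk Intervention), each arm has its own trainer (Control Intervention), in-clinic sessions for the two arms are held at different times (Limitations), and the analysis takes a cluster size of 3 (Primary Analysis). So the three people who train together are in one arm.

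**How many assignments could be known in advance?** Sample Size Calculation gives 18 + 18 = 36 per site and 72 in all.
- Triplets: 36/3 = 12 per site, 72/3 = 24 overall.
- If the arm is released when the first member enrolls, two of the three places are known: 2 × 12 = 24 of 36 per site, 2 × 24 = 48 of 72 overall.
- Block size governs how hard it is to guess the next triplet. It has no bearing on the places left in a triplet whose arm is already known.

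**What if release works otherwise?** The article states no predictability figure, so there is none to reproduce. The table comes from 20,000 simulated sequences per scenario for one site, with a coordinator who knows past assignments and guesses the arm that is behind (a tie counts as one half). Block sizes are assumptions, because the article rightly does not disclose them. Chance is 50%.

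| Reading of the text | Assumed blocks | Correct guesses |
|---|---|---|
| (a) Three enrolled people assigned together | one block of 12 triplets | 64% |
| | 2, 4 or 6 triplets | 71% |
| | 2 or 4 triplets | 73% |
| | 2 triplets, fixed | 75% |
| (b) Members assigned one by one into a triplet sharing an arm | same range | 88% to 92% |
| (c) Individuals randomized separately, 36 per site | 6; 6 or 12; 2, 4 or 6; 4, 6 or 8 people | 66% to 71% |

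Row (b) follows from row (a): with g the chance of guessing a triplet, the share per person is (g + 2)/3. This gives (0.643 + 2)/3 = 0.88 and (0.75 + 2)/3 = 0.92.

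Under (a) and (c) guessing beats chance but is never certain from a fellow member's arm. In all three rows the advantage exists because the person who screens is told past assignments.

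**Who asks about falls between visits?**

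| Period | Person named | Knows the arm? |
|---|---|---|
| Unsupervised phase (visits at weeks 5 and 10) | Trainer, weekly | Yes, delivers it |
| Week 10 to week 62 | Site coordinator, monthly | Yes, obtained it |

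The second period is 62 − 10 = 52 of 62 weeks, or 84% of the calendar time. That is a share of time and not of falls data, since the Fall Calendar may be completed by the participant. No one unaware of the arm is named as collecting or classifying falls between visits.

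**The case against.** Obtaining an assignment from a central list after enrollment, with undisclosed variable blocks, is ordinary practice. Whether a triplet is filled before release is an operational detail that an article may leave to the full protocol, and the flowchart cited alongside the timing of randomization is not shown. Coordinators have limited room for selection: they apply a questionnaire to one age band, a physician clears the rest, and most other criteria are fixed scores or facts. The monthly contacts are presented as a way to limit loss to follow-up, and falls are a tertiary outcome.

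Most of this stands, and it limits the point. Four stronger readings are tempting, and the article supports none of them.
- **That 48 of 72 assignments are predictable.** This needs reading (b). The singular wording suggests it but does not settle it, and joint assignment of three enrolled people is neither stated nor excluded.
- **That falls follow-up contradicts the blinding statement.** That statement is tied to four scheduled visits. The article nowhere claims that the contacts between visits are blinded.
- **That baseline is measured after allocation.** The text does not fix the order, the missing flowchart may, and baseline is in any case measured by blinded evaluators.
- **That the Two-Minute Walk Test is unblinded.** Nothing in the article gives the evaluators the arm.

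What the objection does not remove is the overlap itself. One role screens, is told the arm and then asks about falls, and this is stated text that needs no inference.

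**Conclusion.** The point holds as an avoidable weakness in conduct, not as a proven breach of concealment or blinding. If assignments are released before a triplet is full, up to 48 of 72 arms are known to someone who screens. The number actually open to influence would be smaller, because coordinators screen only part of the entrants and some triplets may be screened together. If triplets are filled first, a coordinator told past assignments still guesses the next one correctly about 64% to 75% of the time under the assumed block sizes. For falls, the named sources between visits all know the arm. The size of any resulting bias cannot be derived from the article. The falls risk is confined to a tertiary outcome and leaves the primary outcome and the other visit-based outcomes alone; a selection effect, if it occurred, would not be confined in that way.

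**What to change.** **Trial Design.** State that the statistician releases a triplet's assignment only after all three members are screened, consented and baseline-tested, and sends it directly to the trainer concerned and not to the coordinator who screens. Contact details should reach the trainer by the same route, so that forwarding them does not disclose the arm.

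**Tertiary Outcome Measures and Limitations.** State that between-visit falls are collected and classified for the outcome by someone not told the arm. The coordinator can fill this role once assignments no longer pass through that office. It should not go to the evaluators who measure the Two-Minute Walk Test, because repeated calls would give participants more chances to reveal their arm before the week-62 visit. The trainers' weekly safety calls need not change.

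**Cost.** The first member of a triplet waits for it to fill, which group training in threes already requires. A coordinator may still occasionally learn an arm from a participant, since participants are told to report symptoms to that role (Safety). The article reports no one enrolled yet, so both changes can be made before the first assignment.

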**Figure 1 figure1:**
[figure not shown]
Study Flowchart.

### Participants

A total of 72 community-dwelling prosthetic ambulators in London and Vancouver will be recruited through clinicians and prosthetists. A letter of information will be distributed to all individuals in the amputee program databases who meet the study inclusion criteria. Participants need to be ≥50 years of age, have a unilateral TT or TF amputation, use their prosthesis for at least 2 hours per day for the past 6 months to minimize the influence of residual limb/prosthetic fit problems, be cognitively able to engage in the program (receive a score on the Modified Mini-Mental Status Exam score of >23) [31], and have a television that will enable connection to the Nintendo hardware.

Individuals will be excluded if they cannot communicate in English, cannot provide informed consent, have medical conditions (eg, congestive heart failure) that limit exercise participation as determined using the American College of Sports Medicine exercise guidelines for older adults [32], have prosthetic fit issues (eg, pain and discomfort) as indicated by scores <6 on the Prosthetic Socket Fit Comfort Scale [33], or are currently participating in another supervised exercise or training program (eg, balance training).

Participants between 50-69 years old will be medically screened by the site coordinators using the Physical Activity Readiness Questionnaire (PAR-Q) [34]. Participants who are 70 or more years old or who answer “yes” to any of the PAR-Q questions will be medically screened by a physician using the Physical Activity Readiness Medical Examination (PARmed-X) to obtain clearance for physical activity participation [35].

